### Sample size calculation

In this study, the sample size was determined using a multiple group mean comparison method. The sample calculation formula is $$n = {\varphi ^2}\left( {\sum {S_i^2/g} } \right)/\left[ {{{\sum {\left( {{{\bar X}_t} - \bar X} \right)} }^2}/\left( {g - 1} \right)} \right]$$

The number of groups(g) is three, and the number of participants in the control and ccPAS low-frequency groups and the ccPAS high-frequency group was 1:1:1. α is the probability of rejecting a true null hypothesis, α is set to 0.025. β is set to 0.1, power(1-β) is the probability of rejecting a false null hypothesis. K is the group means multiplier; k is 1. The value of φ is obtained by checking the table according to α, β, v1, v2.According to previous studies, the three group means are set to 8.11 6.87 17.62, the within group standard deviation (σ) is 8.83 [43]. Using PASS 15 analysis, we get that the total sample size is 54 and the sample size of each group is 18. Considering the 20% dropout rate, the total sample size of the study should be set to 69 and the sample size of each group is 23.

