## Methods and analysis

### Study design

This study is a double-blind randomized controlled trial, and the protocol is registered with the Chinese Clinical Trials Registry. A total of 69 participants will be divided 1:1:1 into three groups. The control group will receive conventional treatment plus sham ccPAS, the ccPAS low-frequency group received conventional treatment plus 0.2 HZ of ccPAS, and the ccPAS high-frequency group will receive conventional treatment plus 5 HZ of ccPAS.

Each group will receive the intervention five times per week for two weeks. The researcher will follow up with subjects in week six and week fourteen respectively (as shown in Fig. 1 and Table 1).T The primary outcome measure will be the ‘Fugl-Meyer Assessment of the Upper Extremity (FMA-UE)’, secondary outcomes will include ‘The line bisection test’, ‘Modified Taylor Complex Figure (MTCF)’, ‘NIH stroke scale (NIHSS)’, and’ functional Magnetic Resonance Imaging(fMRI)’ as well as ‘Diffusion tensor imaging (DTI)’.

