### Fugl-Meyer assessment of the upper extremity (FMA-UE)

The Fugl-Meyer Assessment (FMA) is a widely used method for evaluating sensorimotor impairment in stroke patients and is commonly employed in the clinical assessment of motor function [52]. The Fugl-Meyer Assessment scores have been tested repeatedly and have shown good consistency, responsiveness, and accuracy. The FMA-UE contains 33 assessment items with a total score of 66. The testers can rate the severity of the subject’s motor impairment based on their final score.

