### Statistical analysis

#### Behavior statistical analysis

IBM SPSS Statistics 25.0 will be used to analyze the measurement data for each of the three groups at four time points. Measures will be tested for normality, and those meeting the normal distribution will be expressed as mean ± standard deviation (x ± s). Within-group comparisons, post-intervention and two follow-up visits will be compared with baseline (first assessment) using ANOVA with repeated measures data, and then two-by-two comparisons (post-hoc) will be performed to observe differences at each time point if the overall difference was statistically significant. One-way ANOVA will be used for comparison between groups, and further two-by-two comparisons were made. Measures that do not pass the normality test will be expressed as marginal, maximum, and minimum values. Non-normally distributed measures will be compared by Friedman test for a group of own pre-post comparisons and Kruska-Walls H test for between-group comparisons. The level of unity significance will be set at P = 0.05, and P < 0.05 is statistically significant.

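### The sample size inputs are not identified as FMA-UE scores or changes, so the stated 90% power is not shown to apply to the between-group ANOVA as written

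*Protocol article*

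**What the plan says.** All places are in the protocol article.

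- *Study design*: "A total of 69 participants will be divided 1:1:1 into three groups". FMA-UE is the primary outcome.
- *Sample size calculation*: "α is set to 0.025", "β is set to 0.1, power(1-β) is the probability of rejecting a false null hypothesis", and, taken from previous research, "the three group means are set to 8.11 6.87 17.62, the within group standard deviation (σ) is 8.83". The result is that "the total sample size is 54 and the sample size of each group is 18", raised to 23 per group for 20% dropout. The section does not say which outcome the means and SD describe, whether they are scores or changes, or at which visit.
- *Fugl-Meyer assessment of the upper extremity*: "The FMA-UE contains 33 assessment items with a total score of 66".
- *Behavior statistical analysis*: the section opens by referring to measurements in the three groups at four time points. Baseline is mentioned only for the within-group comparisons. For the arms it says: "One-way ANOVA will be used for comparison between groups, and further two-by-two comparisons were made". No change score or baseline adjustment is named. The significance rule is: "The level of unity significance will be set at P = 0.05, and P < 0.05 is statistically significant".

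**The concern.** A power figure belongs to one variable with one SD. Here the variable behind the calculation is unnamed, and the variable that the analysis section appears to compare is probably a different one.

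Taken as scores, two of the three means are smaller than the SD on a scale that starts at zero. Means of 7 to 8 out of 66 would also describe a very severely impaired sample. The eligibility criteria set no motor-severity limit, and stimulation intensity is set during mild voluntary contraction of a hand muscle. Taken as changes from baseline, the numbers look natural. But 8.83 is then the SD of a change, while the between-group test, read plainly, uses the visit score. When severity is unrestricted, the spread of the score between patients can be much larger than the spread of a change over a two-week intervention.

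At stake is how a non-significant primary result would be read: as coming from a trial with 90% power, when the test actually run may have had much less.

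**Working it through.** **1. Reproduce the plan's figure.** Inputs from *Sample size calculation*: means 8.11, 6.87, 17.62; SD 8.83; alpha 0.025; three equal groups.

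- Grand mean = (8.11 + 6.87 + 17.62)/3 = 10.867.
- Sum of squared deviations = 7.599 + 15.973 + 45.608 = 69.180.
- Noncentrality λ = n × 69.180 / 8.83² = n × 69.180 / 77.969. For n = 18, λ = 15.97.
- Noncentral F power with 2 and 3n − 3 degrees of freedom: n = 18 gives 0.902 and n = 17 gives 0.881, so 18 is the smallest n reaching 0.90.
- Dropout: 18/0.8 = 22.5, rounded up to 23 per arm, 69 in total.

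The arithmetic is correct. At the analysis alpha of 0.05, the same 18 per arm gives 0.945.

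**2. Read the inputs as scores.** Under a normal model with SD 8.83, the share below zero is Φ(−mean/8.83):

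| Mean | Share below 0 | Largest SD possible on 0-66, √(mean × (66 − mean)) |
|---|---|---|
| 8.11 | 18% | 21.7 |
| 6.87 | 22% | 20.2 |
| 17.62 | 2% | 29.2 |

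The values are possible on the scale, but not as roughly normal scores in the two lower arms.

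**3. Read the inputs as changes.** Randomisation makes the expected baseline equal across arms, so the differences between arms are the same for score and change, and only the SD differs. With equal variance at both visits and baseline-to-visit correlation ρ, the change SD is score SD × √(2(1 − ρ)). Hence score SD = 8.83/√(2(1 − ρ)). The document gives neither ρ nor a score SD, so the ρ values below are assumptions.

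Power of the raw-score one-way ANOVA, 18 per arm:

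| ρ | Score SD | alpha 0.025 | alpha 0.05 |
|---|---|---|---|
| 0.5 | 8.83 | 0.90 | 0.94 |
| 0.7 | 11.40 | 0.67 | 0.77 |
| 0.8 | 13.96 | 0.47 | 0.59 |
| 0.9 | 19.74 | 0.23 | 0.32 |

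If all 23 per arm are evaluable and alpha is 0.05, ρ = 0.8 gives 0.71 and ρ = 0.9 gives 0.41.

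**4. Baseline adjustment under the same assumptions.** The ANCOVA residual SD is score SD × √(1 − ρ²) = 8.83 × √((1 + ρ)/2), which never exceeds 8.83. At ρ = 0.9 it is 8.61. With one further degree of freedom spent, power with 18 per arm at alpha 0.025 is 0.92. At ρ = 0.7 it is 8.14, and power is 0.95.

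**The case against.** The strongest reply has four parts.

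- *The inputs are not impossible as scores.* This stands. A reader might infer that these means and SD cannot be FMA-UE scores. The document does not support that: all three means lie within 0-66, the SD is attainable at each, no criterion excludes a severely impaired sample, and the negative tail comes from the normal model. The plan also provides a rank-based test for non-normal data. Implausible as approximately normal scores is as far as it goes.
- *The between-group sentence names no variable.* This stands in part. It does not rule out a change score, and a condensed article may leave that detail to a fuller document. But the section speaks of measurements at each time point and uses baseline only within groups, so the plain reading is a comparison of visit scores. The article chose to print both the inputs and the test, and nothing printed connects them.
- *A larger score SD is assumed.* This stands. At ρ = 0.5 there is no loss, and below 0.5 the raw score is the more precise variable. A reader might infer that the trial is underpowered as a fact. That is not established.
- *Alpha 0.025 exaggerates the shortfall, because the analysis tests at 0.05.* This is correct, and it is why both are shown. The loss is smaller at 0.05, but it remains for ρ of 0.7 and above.

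**Conclusion.** The point holds as a missing link between the power calculation and the planned test, not as an arithmetic error. The sample size is computed correctly for a variable with SD 8.83, but the protocol does not say what that variable is. The more natural reading (change from baseline) is not what the analysis section appears to compare.

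The size of the loss is conditional on three things: 8.83 being a change SD, equal variance at both visits, and the assumed correlation. Under those conditions, power with 18 per arm runs from 0.90 at ρ = 0.5 down to 0.23 at ρ = 0.9 (alpha 0.025), or from 0.94 down to 0.32 (alpha 0.05). A correlation well above 0.5 is a reasonable expectation in patients 3 to 12 months after stroke, with no severity limit and a two-week intervention, but the document does not give one.

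This is more than a labelling matter. Run as written, the raw-score ANOVA ignores a baseline FMA-UE that is already collected, and it loses power to the extent that baseline predicts outcome.

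**What to change.** 1. In *Sample size calculation*, state the outcome, the scale (score or change from baseline) and the visit to which the three means and the SD refer.
2. In *Behavior statistical analysis*, make the between-group comparison of FMA-UE at the end of the intervention an ANCOVA adjusted for baseline FMA-UE. At the least, name change from baseline as the compared variable. If 8.83 is a change SD, either choice keeps power at or above 0.90 with 18 per arm at alpha 0.025, under the equal-variance assumption for the ANCOVA.
3. If the unadjusted visit score is kept, replace 8.83 by the SD of that score and restate the power.

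The cost is wording in two sections or, under item 3, possibly a lower stated power. No participants, visits or assessments are added. The change should be made before the data are unblinded.

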### Randomization and allocation concealment

A random number table will be generated by SPSS 25.0 to create random assignment cards. These cards will then be placed in opaque envelopes with envelope serial numbers connected to the card serial numbers. Participants will be randomly assigned codes based on the order in which they are seen. The grouping specified by the card inside the envelope will determine which group each participant will be assigned to, with each group consisting of 23 participants: a control group, a ccPAS low-frequency group, and a ccPAS high-frequency group. The grouping information will be kept confidential from the patients, their families, therapists, evaluators, and statistical analysts. Patient treatment information will be sent to the researcher one day prior to the treatment.

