## Abstract

**Introduction:**

: Brain has a spontaneous recovery after stroke, reflecting the plasticity of the brain. Currently, TMS is used for studies of single-target brain region modulation, which lacks consideration of brain networks and functional connectivity. Cortico-cortical paired associative stimulation (ccPAS) promotes recovery of motor function. Multisensory effects in primary visual cortex(V1) directly influence behavior and perception, which facilitate motor functional recovery in stroke patients. Therefore, in this study, dual-targeted precise stimulation of V1 and primary motor cortex(M1) on the affected hemisphere of stroke patients will be used for cortical visuomotor multisensory integration to improve motor function.

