### Inclusion criteria

Stroke (Infarction/Ischemia) [40];Age ≥ 40 years and ≤ 70 years, regardless of sex [41];Time of onset ≥ three months and ≤ 1 year;right-handedness;normal cognitive function (MMSE above the threshold corresponding to different cultural levels);Informed consent;

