Previous research has demonstrated that the primary visual cortex plays a role in multisensory processing during the early stages of stimulation. Furthermore, it has been shown that multisensory effects within this region directly impact behavior and perception, which can aid in motor function recovery [38]. By directly intervening with ccPAS in both V1 and M1 to achieve multisensory integration in the brain, we can further clarify the correlation between connectivity among brain regions and verify the effects of interactions between different brain networks on brain plasticity.

It is expected that the combination of ccPAS and the concept of multisensory integration will be effective in promoting the recovery of motor function, enhancing the functional connectivity of damaged motor neural circuits after stroke, and providing a new therapeutic option for chronic post-stroke rehabilitation.

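### Time since stroke onset (3 to 12 months) is used in neither the allocation nor the stated between-arm ANOVA of FMA-UE; this costs precision but causes no bias, and one prespecified model term recovers it

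*Protocol article*

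**What the plan says.** Under Inclusion criteria the Protocol article sets the window "Time of onset ≥ three months and ≤ 1 year". The section Randomization and allocation concealment describes one procedure: "A random number table will be generated by SPSS 25.0 to create random assignment cards", the cards go into numbered opaque envelopes, and "Participants will be randomly assigned codes based on the order in which they are seen". Arm sizes are fixed, "with each group consisting of 23 participants", in line with Study design: "A total of 69 participants will be divided 1:1:1 into three groups". No stratification or minimisation factor is named.

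Behavior statistical analysis compares the three arms by one-way ANOVA followed by pairwise comparisons, with a Kruskal-Wallis test for measures that fail a normality test. No covariate is named.

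The Abstract opens with "Brain has a spontaneous recovery after stroke, reflecting the plasticity of the brain". Nothing in the article says how recovery varies between month 3 and month 12.

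**The concern.** The window is wide: the latest eligible patient is four times as far from onset as the earliest. The article itself recognises spontaneous recovery, so time since onset is a plausible predictor of FMA-UE over the follow-up. With 23 patients per arm, a visible imbalance in this factor is quite possible, and the stated analysis has no term that would absorb it.

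Two things are at stake. The first is precision: whatever variance the factor explains stays in the ANOVA error term. The second is credibility: if an imbalance appears at baseline, an adjustment chosen after seeing it carries less weight than one fixed in advance.

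**Working it through.** **Inputs from the article (Sample size calculation).** Three arms; assumed means 8.11, 6.87 and 17.62; within-group SD 8.83; power 0.90; "α is set to 0.025"; 18 evaluable and 23 randomised per arm. All power figures below use alpha 0.025. The analysis section tests at 0.05, which is a separate discrepancy.

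**Assumed inputs (not in the documents).** Time since onset is uniform on 3 to 12 months and explains a share R² of FMA-UE variance, taken as 5%, 10% or 25%.

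**1. The plan's own figure.** The grand mean is 32.60/3 = 10.867. The squared deviations sum to 7.60 + 15.97 + 45.61 = 69.18. The noncentrality is n × 69.18/8.83². For n = 18 it is 18 × 69.18/77.97 = 15.97, and the noncentral F distribution with 2 and 51 degrees of freedom gives power 0.902; n = 17 gives 0.881. Then 18/0.8 = 22.5, rounded up to 23 per arm, 69 in total. The stated sample size reproduces.

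**2. How large a chance imbalance can be.** The SD of onset time is 9/√12 = 2.60 months. The SD of the difference in means between two arms of 23 is 2.60 × √(2/23) = 0.77 months, so 95% of trials fall within about 1.5 months. If one third to one half of patients count as early (3 to 6 months after onset, say), the early share differs between two given arms by up to 26 to 30 percentage points in 95% of trials (simulated).

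**3. What that means in FMA-UE points.** The 95% limit of the shift between two arms is 1.96 × √R² × 8.83 × √(2/23):

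| R² | 95% limit (points) |
|---|---|
| 5% | 1.1 |
| 10% | 1.6 |
| 25% | 2.6 |

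The total 95% sampling error of a two-arm difference is 1.96 × 8.83 × √(2/23) = 5.1 points, and this shift is part of it. The assumed differences are 17.62 − 8.11 = 9.51, 17.62 − 6.87 = 10.75 and 8.11 − 6.87 = 1.24.

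**4. Type I error without stratification.** The simulated rate (8,000 runs per cell) for the unadjusted ANOVA at nominal 0.05 is 0.044 to 0.057, with 18 or 23 per arm and R² of 0, 10% or 25%. There is no inflation beyond simulation noise.

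**5. Power and type I error by strategy, 18 evaluable per arm (simulated; two strata split at 6 months, blocks of 3).**

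| Strategy | Power, R² 10% | Power, R² 25% | Type I error at 0.05, R² 10% / 25% |
|---|---|---|---|
| No strata, unadjusted | 0.90 | 0.90 | 0.050 / 0.053 |
| Strata, unadjusted | 0.90 | 0.91 | 0.039 / 0.028 |
| No strata, adjusted | 0.93 | 0.97 | 0.049 / 0.048 |
| Strata, adjusted | 0.93 | 0.97 | 0.049 / 0.051 |

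A direct calculation agrees. Dividing the noncentrality by 1 − R² gives 15.97/0.90 = 17.75 and 15.97/0.75 = 21.29; with 2 and 50 degrees of freedom the power is 0.932 and 0.969. At R² = 5%, 15.97/0.95 = 16.81 gives 0.917. At R² = 0 the lost degree of freedom moves power only from 0.902 to 0.901.

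If nobody drops out (23 per arm), the simulated gain is smaller in absolute terms: from about 0.966 to 0.978 (10%) or 0.994 (25%).

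**The case against.** The strongest reply is that randomisation already deals with this. Chance imbalance in a prognostic factor is part of the error that the P value measures, and step 4 bears that out. A reader might infer from the wide window and the unstratified list that uneven natural recovery biases the trial, or that it could pass for or hide a treatment effect. The documents do not support that. Allocation is random, the error rate is nominal, and a shift of 1.1 to 2.6 points neither creates nor hides a planned gap of 9.51 or 10.75. It is comparable only with the 1.24-point gap between the two lower means, which the trial cannot resolve anyway. Nor is a material imbalance likely: a gap of at least 5 of 23 early patients (22 percentage points) arises between some pair of arms in 33% to 38% of trials, and in a given pair in 16% to 19%.

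It is also fair to say that stratifying 69 patients is discretionary, that the article limits the factor by excluding patients outside 3 to 12 months, and that covariates are often left to an analysis plan. The first two points stand. The third stands only in part. The article is not silent: it names an unadjusted method, and a better one is available at almost no cost. A full protocol or analysis plan may already name the covariate, in which case the point falls away.

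One further reading is tempting. The Discussion hopes for "providing a new therapeutic option for chronic post-stroke rehabilitation", and a reader might say that the trial cannot support this without a split by time since onset. That sentence states an expectation, not a conclusion, and the article never defines chronic by a number of months, so no contradiction can be drawn.

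What remains on the other side is conditional. Given that a pair of arms does differ by at least 5 early patients (one third early), the unadjusted test of that pair at nominal 5% rejects falsely in about 5% to 6%, 8% or 12% of cases if early patients gain 3, 6 or 9 points more (assumed; simulated). This does not contradict the nominal overall rate. It shows why a prespecified adjustment is worth having.

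**Conclusion.** The point holds as a minor matter of efficiency and credibility. A variable already collected for eligibility, and plausibly prognostic on the article's own account, is left out of both the allocation and the stated FMA-UE comparison. The cost is lost precision and an uncorrected imbalance if one occurs.

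The size rests on an assumed strength of association, because the documents give none. The power gain is about 3 percentage points at 10% of variance and 7 at 25%, about 1.5 at 5%, and nil if the factor is not prognostic. The sample size is not in question. Nearly all of the benefit comes from the model term; stratified lists combined with the planned unadjusted ANOVA leave power at 0.90 to 0.91 and make the test conservative.

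**What to change.** In Behavior statistical analysis, replace the between-group one-way ANOVA of FMA-UE with a prespecified ANCOVA that includes months since onset as a covariate, fixed before any unblinded look at the data. This can be done whether or not enrolment has started.

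If enrolment has not begun, the envelope lists may also be generated in permuted blocks within strata of time since onset, with that stratum kept in the model. Stratification without the model term is not worthwhile.

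The cost is one degree of freedom and no new data. If the lists are stratified, there is a second envelope series to manage, and final arm sizes may differ from 23 by one or two.

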### Blinding

Each participant will sign a written confidentiality agreement to ensure that information is not shared with others. Randomization of patients will be done remotely by a person who will not be involved in the rest of the trial process. Patients who meet the inclusion criteria will undergo a first basic assessment by a person dedicated to the assessment after signing the informed consent form.

Routine rehabilitation will be done by a physical therapist, an occupational therapist, and a speech therapist in the rehabilitation medicine department. ccPAS treatment will be done by a dedicated researcher, following the given parameters.

The two-week post-intervention assessment will be completed by a second assessor. Follow-up will be done by a third assessor. The data from all assessments will be analyzed by a dedicated data analyst, who will only be provided with the data results for each group without knowing the specific group allocation.

